**IRB approval status:**

MEC-2018-093.

Strengths and limitations of this studyPatient and observer blinded randomised controlled design.Both patient-reported outcomes and objective functional test outcomes will be measured.Inclusion of an economic evaluation.Instability as outcome may not be measurable in 2 years of follow-up.Diversity in terminology on posterior decompression techniques may lead to variability on both surgical techniques.

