## Introduction

Lumbar spinal stenosis (LSS) is described as the narrowing of the diameter of the spinal and nerve root canals, which can cause compression of the neural structures in the canals.^1^ LSS is a common medical condition in the ageing population and is considered the most common reason for lumbar spine surgery for people over the age of 65.^2–4^ Intermittent neurogenic claudication (INC) is the most important symptom of LSS, with leg pain and heaviness of the legs, usually bilateral, which exacerbate during standing and walking. Apart from leg pain, back pain is often also present.^5^ As the symptoms aggravate, the ability to walk can become considerably limited, which is the dominant functional impairment and the most common reason for seeking medical care.^6 7^

Conservative treatment, such as physical therapy and pain medication, is the first treatment option and may give some relief of symptoms.^8^ Previous research shows that there is sparse evidence of the effectiveness of surgery compared with non-operative treatment.^9^ However, usually when conservative treatment fails, surgical treatment is considered the next option.^10 11^ The first technique described to widen the lumbar spinal canal is the laminectomy technique, also known as wide bony decompression, which is a widely used surgical technique for patients with INC caused by LSS.^12^ Given that patients often experience postoperative back pain after laminectomy, it is hypothesised that laminectomy is a ground for potential lumbar instability and iatrogenic scoliosis.^13–15^ Performing a procedure with potentially more complications in an elderly population could be considered as doubtful. Hence, less invasive techniques, such as the bilateral small size interarcuair decompression, otherwise known as a bilateral laminotomy, limited bony decompression or interlaminar decompression, were developed and implemented in clinical practice. These techniques require less bone tissue to be removed, which possibly can reduce the prevalence of lumbar instability in these patients and consequently improve functioning.^16^ Furthermore, it is believed that, compared with laminectomy, these less invasive techniques have the ability to decompress the nerves while preserving the spinal integrity. However, the risk of an insufficient decompression may be higher, possibly resulting in reoperations due to residual stenosis.^16–18^

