##### Physical examination

A physical examination will be performed before surgery, at 6 weeks, 12, 24 and 48 months after surgery. This examination will include a brief neurological examination, the Timed Up and Go Test (TUG), the Timed Chair-Stand Test (TCST), the 6-Minute Walking Test (6MWT) and patient’s weight.

Neurological examinationThe neurological examination will include the muscle strength of the quadriceps, the iliopsoas, the hamstrings, the gastrocnemicus and the tibialis anterior muscle, which will be noted as a difference in strength between both legs. We will evaluate if there is a difference in muscle strength between the affected leg and the other leg.TUGPatients are asked to sit in a chair with their arms resting on the armrests. On direction of the research nurse, patients have to walk as fast as possible (without running) to a wall at 3 m distance of the chair. When they have reached that wall, a turn of 180° is made and they walk directly back to the chair and sit down. The research nurse will measure the time(in seconds) it takes for a patient, to perform this action. The time is stopped when the patients are seated again.^33^ Patients need to perform this test, three times. Patients are allowed to wear their regular shoes and use a walking aid, if necessary. The TUG test has been described as a valid, reliable tool in the assessment of objective functional impairment in patients with lumbar degenerative disc disease.^34 35^ However, this has not been done for LSS. The validation for LSS will be conducted in this study.TCSTPatients are asked to sit down on an armless chair, firmly placed against a wall, with their arms folded across their chest. They are instructed to place their feet flat on the ground. To become familiarised with the exercise, the patients are asked to stand up and sit down again without using their arms. If assistance is required during this action, or this movement cannot be completed by the patient, the test is abandoned. If the manoeuvre is possible, the patient will be asked to, on the word ‘go’, stand up entirely and sit down again, five times as quick as possible. The research nurse will time the five movements in seconds from the command ‘go’ to the completed fifth stand. The measured time will be noted as the score. If the patient is unable to perform the test five times, a maximum score will be noted of 30 s.^36^
^37^

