6MWTThis test is performed to assess the gait pattern, walking speed and physical endurance of patients. The patient will be requested to walk at such a speed that at the end of 6 min, the patient will have the feeling of maximum output.^38^ Before taking the test, the patient will be given the instructions to install the 6MWT application on their cell phone.^39 40^ During these 6 min this application will measure the walking distance. During the walking test, the patient is permitted to use a walking aid and/or orthosis which will be noted.

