### Statistical analysis

Patient characteristics will be summarised per treatment group to determine whether the randomisation was balanced. Continuous variables will be presented using means and SDs, or in the case of non-normally distributed variables using medians and IQRs. Normality will be graphically assessed. Categorical variables will be presented using counts and percentages. The primary analysis will study differences in the primary outcome measure (RMDQ). The primary endpoint of interest is 12 months after randomisation. The results of the RMDQ will be assessed using generalised linear mixed models (GLMM), to account for the repeated measurements within patients and the multicentre stratification.

The secondary outcomes (ODI, NRS leg and back pain score, TUG test, TCST and the SF-36) will be similarly assessed using GLMMs and will be analysed for exploratory purposes. In all analyses the primary assessment of treatment effect will be the estimate of the main effect within the appropriate model at 12 months, adjusted for the stratification factors and main covariates. Time to recovery will be analysed using survival analysis (Cox proportional hazards). At 24, 36 and 48 months, the GLMM repeated-measurement analyses using the compound symmetry covariance structure will be used while *group* (interarcuair and conventional), *time* (moments of measurement) and the *interaction* between group and time (grou×time) will be entered as independent variables. Dependent variables are the primary and secondary outcome parameters. Likert scales for self-reported patient recovery and satisfaction will be assessed using descriptive statistics (counts and percentages) and appropriate plots. Comparisons of Likert scale results at individual time points will be tested using Mann-Whitney U tests. Complications and incidence of reoperations will be assessed using descriptive statistics (counts and percentages). Comparisons between treatment groups for specific complications of interest will be assessed using Χ^2^ tests or Fisher’s exact tests. If necessary, missing data will be imputed using multiple imputation techniques.

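### The 6-minute walk, the trial's only performance test of walking distance or endurance, is measured on each patient's own phone and is missing from the named 12-month analysis list

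*Protocol article*

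**What the plan says.** All references are to the protocol article.

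- **Introduction.** As symptoms of stenosis progress, "the ability to walk can become considerably limited, which is the dominant functional impairment and the most common reason for seeking medical care".
- **Physical examination (under Secondary outcomes).** The examination includes the Timed Up and Go test (TUG), "the Timed Chair-Stand Test (TCST), the 6-Minute Walking Test (6MWT) and patient’s weight". On timing: "A physical examination will be performed before surgery, at 6 weeks, 12, 24 and 48 months after surgery". Table 1 agrees and places a research nurse visit at each of these five points.
- **6MWT.** "Before taking the test, the patient will be given the instructions to install the 6MWT application on their cell phone". Then: "During these 6 min this application will measure the walking distance". The article mentions no study device, measured course or alternative for a patient without a suitable phone. For the TUG and the chair-stand test (TCST), by contrast, the research nurse does the timing, and the TCST has a set score for patients who cannot finish.
- **Statistical analysis.** "The secondary outcomes (ODI, NRS leg and back pain score, TUG test, TCST and the SF-36) will be similarly assessed using GLMMs". These analyses are labelled exploratory, and the main treatment estimate is taken at 12 months. A later sentence, on the 24, 36 and 48 month models, takes all primary and secondary outcomes as dependent variables without listing them.
- **Strengths and limitations.** Among the strengths: "Both patient-reported outcomes and objective functional test outcomes will be measured".

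**The concern.** Two stated choices weaken the test that lies closest to the disease.

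The first is the measuring device. Phone ownership is likely to vary with age, and the section on cost diaries expects an elderly, partly retired population. Patients without a usable phone would be missing at every examination rather than at scattered visits. A repeated-measures model would then have no walking value of the patient's own to borrow from, and imputation would have to rely on other variables. Among patients with a reading, differences between handsets add error to the comparison of distances. A handset replaced between intake and a later visit adds error to the change from intake.

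The second is the list. Three functional tests share one examination and one schedule. Two are named for the 12-month model and the third is not. With no stated place in the 12-month analysis, the 6MWT result could be modelled, described or left out after the data are seen.

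At stake is how well the trial can support its claim to objective functional outcomes where walking is concerned. The primary outcome, the Roland-Morris questionnaire, is not affected.

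**Working it through.** **1. The plan's own figure.** The article gives no sample size for the 6MWT. Its only calculation is for the Roland-Morris score: difference 3, SD 6, alpha 0.05, power 90%, 69 per group. With n = 2(z_alpha + z_power)² × (SD/difference)²:
- one-sided 0.05: 2 × (1.645 + 1.282)² × 4 = 68.5, so 69;
- two-sided 0.05: 2 × (1.960 + 1.282)² × 4 = 84.1, so 85.

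The stated 69 is the one-sided result, and 69 / 0.8 = 86.25, so 87 per group and 174 in total. This sets the number of patients available but says nothing about the precision of the 6MWT.

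**2. The sections side by side.**

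| Test | Examined at 12 months | How measured | Named for the 12-month model |
|---|---|---|---|
| TUG | yes | timed by research nurse | yes |
| TCST | yes | timed by research nurse | yes |
| 6MWT | yes | application on patient's phone | no |

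The TUG involves a 3 m walk out and back, so it reflects short-distance speed. Neither it nor the TCST measures distance or endurance.

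**3. Patients without a reading (assumed range).** The article gives no rate of phone ownership. If 10% to 30% have no usable phone:
- 174 × 0.10 = 17.4, about 17;
- 174 × 0.30 = 52.2, about 52.

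These patients would have no 6MWT at any of the five examinations, before other losses.

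**4. Device error (assumed range).** If handset differences add variance equal to a fraction k of the between-patient variance, the effective sample for a single score shrinks by 1 − 1/(1 + k):
- k = 0.10: 1 − 1/1.1 = 9%;
- k = 0.30: 1 − 1/1.3 = 23%.

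This applies to a single score. In a change from intake, a stable error from one handset cancels, while the error from a change of handset does not.

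**5. What this could do to power (illustration).** Assume 69 evaluable patients per group, a true standardised effect of 0.5 and two-sided alpha 0.05. Power = Φ(0.5 × √r × √(n/2) − 1.96), where r is the reliability of the reading, r = 1/(1 + k).

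| Missing readings | n per group | r | Power |
|---|---|---|---|
| none | 69 | 1.0 | 0.84 |
| 10% | 62.1 | 1.0 | 0.80 |
| 20% | 55.2 | 1.0 | 0.75 |
| 30% | 48.3 | 1.0 | 0.69 |
| 20% | 55.2 | 0.8 | 0.65 |

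None of the missing rates, reliabilities or the 6MWT effect size comes from the article.

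**6. Does the loss differ by arm?** Randomisation takes place after the patient is anaesthetised, so phone ownership at intake is settled before allocation. Patients and researchers are blinded afterwards. Nothing in the article links ownership or later replacement of a phone to the arm.

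**The case against.** A reader might infer that walking gets no valid comparison in this trial. The documents do not support that. Phone ownership and handset type are patient characteristics unrelated to allocation, so they widen the interval and narrow the population represented without by themselves shifting the difference between arms.

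A reader might also infer that the 6MWT is never analysed, or that no other test involves walking. The 24, 36 and 48 month models take in every secondary outcome, and the 6MWT sits under that heading. The TUG times a short walk and is on the 12-month list, and the EQ-5D has a mobility dimension.

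Further arguments against are fair:
- The 12-month secondary analyses are exploratory.
- Other secondary items, such as the X-ray findings and the neurological examination, are also absent from the list, so it may not be complete.
- The article condenses a fuller protocol, and a fallback for patients without a phone may be written there.
- The article cites two sources for the application, and nothing in it shows that readings differ between handsets.
- The percentages above are assumptions.

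These limit the size of the point. What stands is what the article itself fixes: distance is read from the patient's own phone, and the list names two of three sister tests.

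**Conclusion.** The point holds as a modest but worthwhile correction. The omission from the 12-month list is the firmer part, because it follows from comparing two sections of the article. The phone method is a stated choice that can lose patients and add error to the only test of walking distance or endurance. The harm is lost precision and representativeness for one exploratory secondary outcome. It is not an invalid contrast, and it has no bearing on the primary result.

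The size is unknown. The 17 to 52 patients rest on an assumed 10% to 30% without a usable phone, and the 9% to 23% loss of effective sample rests on an assumed added error variance of 10% to 30%. The absence of bias between arms rests on randomisation, maintained blinding and phone-related loss that is unrelated to treatment.

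**What to change.** 1. **Measurement.** Have the research nurse, who is already scheduled at each physical examination, obtain the distance by one uniform method at each site: a study-owned phone with the same application, or a marked course.
2. **Analysis.** Add 6MWT distance to the secondary outcomes named for the 12-month mixed model, keeping their exploratory status.
3. **Transition.** For patients already tested on their own phone, record the method at each visit and either keep that method for them or adjust for it. Switching between intake and follow-up would add error to their change score, which is the small downside of the change.

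The cost is one phone or one measured corridor at each of the three sites, a few words in the Statistical analysis section, and an amendment submitted for ethical review. No extra visit or staff is needed.

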##### Functional lumbar X-rays

Functional X-rays will be obtained from all patients. The X-ray will be made standing from Antero-posterior and lateral position to assess spondylolisthesis. X-rays will also be made in maximum flexion and extension position. Degenerative spondylolisthesis is defined as a vertebral slip of at least 3 mm.^41^ After the measurement of the vertebral slip, this will be classified according to the Meyerding classification. This will be obtained at 6 weeks postoperatively, for level verification and for verification of correct procedure and after 2 years postoperatively to look for possible instability.

##### EuroQol-5-dimension-5-levels

The EuroQol-5-dimension-5-levels (EQ-5D-5L) is a validated instrument to assess health-related quality of life. The tool measures five dimensions:

Mobility.Self-care.Pain/discomfort.Daily activities.Anxiety.

Each dimension consists of one item, in which five levels are distinguished (no problems, minor problems, moderate problems, major problems, severe problems, unable to). The Dutch tariff of the EQ-5D-5L will be used to calculate the quality-adjusted life years (QALYs).^42 43^

###### Cost-diaries

Based on a diary with made costs, which will be completed by patients, insight will be obtained in the need for care, working participation and direct and indirect medical cost. Direct medical cost will be estimated on basis of the cost centre method. In addition it is expected that the study population will consist of elderly people who may be retired. For the cost calculation additional costs, such as help in house, transport and help from family will be taken into account.

For an estimation of direct and indirect cost, permission of the patient will be asked to request the total amount of cost incurred during the research period from the insurance company. No consideration by participation in the investigation as compared with daily practice will be deducted. The additional investigational costs include mainly the additional visits to the outpatient clinic.

The patient will be requested to keep a diary for the financial aspects of the consequences of INC and corresponding treatment. The patient will be requested to record the following items:

Visits to general practitioner.Visits to physiotherapist.Visits to specialist.Alternative medicines and devices (eg, rollator).Number of days of hospitalisation.Pain medication; dosage and frequency.Illness-related days of absence at work, if any.Cost of loss production and substitute manpower, if any.Additional travelling expenses on account of INC.Help in house holding.

##### Complication and reoperation incidence

Immediately after surgery, the surgeon will report any perioperative complications such as cerebrospinal fluid leakage, nerve root damage and if the operation was implemented at the wrong vertebral level. Additionally, a systematic assessment of complications (including urinary tract infection, progressive neurological deficit and secondary bleeding) will be carried out by the surgeon and the research nurse shortly after discharge.

Reoperation is considered a bad outcome. The incidence of reoperation as well as perioperative morbidity will be assessed in both groups, using surgical parameters such as blood loss, time of surgery and length of hospital stay.

We used the Standard Protocol Items: Recommendations for Interventional Trials checklist when writing our report.^44^

### Patient and public involvement

No patients involved.

### Sample size

The sample size of this study is calculated for the primary endpoint of group difference in the RMDQ at 12 months. According to literature, results obtained after interarcuair decompression should be 3 points lower on the RMDQ compared with those for the laminectomy group in order to detect superiority.^45^

Hence, the sample size of this study is based on a superiority design, using a delta of 3, an assumed true mean difference of 0 and a pooled SD of 6. Using an alpha of 0.05, and a power of 90%, we calculated a sample size of 69 patients per group. Accounting for a 20% loss in follow-up, we will therefore enrol 174 patients (87 patients per group).

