### Study objectives

The primary objective of this study is to determine whether bilateral interarcuair decompression is more effective than laminectomy in patients with INC caused by LSS. The secondary objective is to evaluate if bilateral interarcuair decompression is more cost-effective than laminectomy.

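### The sample-size inputs contradict the superiority design, and 69 per group gives 90% power only with an undisclosed one-sided 5% alpha; a two-sided 5% test has about 83%

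*Protocol article*

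**What the plan says.** All the inputs are in the Sample size section of the protocol article. Its first paragraph takes from the literature that scores after interarcuair decompression "should be 3 points lower on the RMDQ compared with those for the laminectomy group in order to detect superiority". The next paragraph describes the calculation as "based on a superiority design, using a delta of 3, an assumed true mean difference of 0 and a pooled SD of 6". It continues: "Using an alpha of 0.05, and a power of 90%, we calculated a sample size of 69 patients per group". Allowing for 20% loss, it enrols 87 per group, 174 in all.

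Under Study objectives, the primary aim is "to determine whether bilateral interarcuair decompression is more effective than laminectomy". The Statistical analysis section plans a generalised linear mixed model for the Roland-Morris score (RMDQ), with the endpoint of interest at 12 months and adjustment for stratification factors and main covariates. Neither section says whether the primary test is one-sided or two-sided.

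**The concern.** Two things do not fit together.

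- **The alternative.** Power is the probability of rejecting the null hypothesis when a stated alternative is true. In a superiority trial that alternative is a non-zero difference. The paragraph gives 3 points in one sentence and "an assumed true mean difference of 0" in the next. Only the first can serve as the alternative for the stated objective. A margin paired with a true difference of zero is what one would enter in a non-inferiority calculation.
- **The alpha.** An unqualified alpha of 0.05 in a superiority trial is normally read as two-sided. The stated sample size does not follow from that reading.

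At stake is the reliability of the stated 90% power. A reader who assumes a two-sided test would believe the type II error at 3 points is 10% when it is about 17%. The sidedness of the primary test is also left open in the one place where the article depends on it.

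**Working it through.** **Inputs, all from the Sample size section:** difference 3 points, SD 6, alpha 0.05 (sidedness not given), power 90%, loss 20%. Allocation is 1:1 (Allocation section).

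**Formula (normal approximation, per group):** n = 2 (z_alpha + z_power)² × SD² / difference², with 2 × 36 / 9 = 8 and z_power = 1.2816.

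**1. Reproducing the stated figure**

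- One-sided 0.05: 8 × (1.6449 + 1.2816)² = 68.5, rounded up to **69**. This matches.
- Two-sided 0.05: 8 × (1.9600 + 1.2816)² = 84.06, rounded up to **85**. This does not match. With the t distribution, 85 per group gives 89.99% power and 86 gives 90.3%.
- Loss: 69 / 0.80 = 86.25, rounded up to 87 per group and 174 in total. This matches.

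**2. Does the zero change the number?** The non-inferiority formula replaces the difference in the denominator by margin minus true difference, here 3 − 0 = 3. With one-sided alpha 0.05 it gives the same 68.5. The two calculations are algebraically identical, so the sample size cannot show which was meant, and the zero by itself costs no power.

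**3. Power with 69 evaluable per group, SD 6, true difference 3, unadjusted**

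Standard error = 6 × √(2/69) = 1.0215, and 3 / 1.0215 = 2.937.

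| Test | Normal | t test |
|---|---|---|
| Two-sided 5% | 83.6% | 83.0% |
| One-sided 5% | 90.2% | 89.9% |

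The difference detectable with 90% power in a two-sided 5% test is (1.9600 + 1.2816) × 1.0215 = 3.31 points.

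**4. What 90% two-sided power would need in the same unadjusted comparison:** 85 to 86 evaluable per group. At 20% loss, 85 / 0.80 = 106.25 and 86 / 0.80 = 107.5, so 107 to 108 enrolled per group, or 214 to 216 in total against 174. If none of the planned 87 per group were lost, two-sided power would be 90.6% (t) or 91.0% (normal).

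**5. Effect of adjusting for baseline RMDQ.** Adjustment multiplies the SD by √(1 − r²), where r is the correlation of baseline with 12-month RMDQ. The documents give no r, so these values are assumptions. At 69 per group, two-sided 5%, power is about 86% for r = 0.3, 89% for r = 0.4 and 92% for r = 0.5.

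**The case against.** The strongest reply is that the 90% is correct. The objective is directional, the difference is stated as a lower score in one named group, and a one-sided 5% test delivers 90% with 69 per group. On that view the zero is only the null value, badly described, and the fault is one of wording. This stands as far as it goes: nothing in the article says that the test is two-sided, so the 83% is conditional. It does not remove the contradiction, because a zero called the assumed true difference is wrong for a superiority calculation whichever sidedness applies. Nor does it supply the missing statement that alpha is one-sided.

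A second reply is that 83% describes an unadjusted comparison of completers. The planned analysis is a repeated-measures mixed model with covariates, and multiple imputation if necessary, so it can use data from patients lost before 12 months. Its power may be higher. That is fair, but the gain cannot be quantified from the documents, and the Sample size section does not rely on it.

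A reader might be tempted by three stronger readings, none of which the documents support:

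- *That a non-inferiority formula was used and this lowered the power.* Step 2 shows that it gives the same number as one-sided superiority at 3 points. The whole gap comes from sidedness.
- *That power is practically nil, because 3 points must be exceeded when the truth is zero.* That calculation could not have produced 69 per group, so the article's own figure rules it out.
- *That a null result is meant to be presented later as non-inferiority.* The article states a superiority objective and a superiority design, and has no non-inferiority objective or test.

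**Conclusion.** The point holds as an internal contradiction and an undisclosed assumption. The zero true difference conflicts with the superiority label, with the 3-point difference in the preceding sentence and with the primary objective. The stated 69 per group is arithmetically sound only for a one-sided alpha of 0.05, and the allowance for loss is correct.

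The consequence for power is conditional. If the primary test is two-sided at 5%, power is about 83% rather than 90%, given SD 6, a true difference of 3, 69 evaluable per group and no covariate adjustment. If it is one-sided at 5%, the stated 90% holds. The documents do not settle which applies, so it cannot be said outright that the trial is underpowered against its own plan. They do support saying that the paragraph is wrong as written, and that the stated power cannot be relied on until the sidedness is declared.

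**What to change.** Revise the Sample size paragraph and add one statement to the Statistical analysis section:

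1. State the hypothesised true difference as 3 RMDQ points in favour of interarcuair decompression, and delete the assumed true mean difference of zero.
2. Declare whether the primary test is one-sided or two-sided, and use the same choice in the analysis section.
3. Report the matching power for 69 evaluable per group: about 83% for 3 points if two-sided 5% (90% for about 3.3 points), or 90% for 3 points if one-sided 5%.
4. Consider naming baseline RMDQ as a covariate in the primary model. This would recover some power, to about 89–92% in a two-sided test if the correlation with the 12-month score is 0.4–0.5. Since that correlation is an assumption, it should be justified before any such figure is quoted.

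The cost is a change of wording. No extra patients are needed, but if the two-sided test is chosen, the stated power becomes less favourable.
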